## Method

### Participants and power analysis

The target group are elite, sub-elite, and recreational athletes from four sports (curling, volleyball, i.e., indoor and beach, tennis, and hockey, i.e., floorball and ice hockey). We chose these sports because they are suited to sample comparable short sequences (see primary outcome below) within a game or a competition, as opposed to, for example, soccer. Athletes who are members of the respective Swiss national sport associations will be contacted and offered the opportunity to participate. Criteria for exclusion are a likely mental disorder, significant previous experience with PST or MI, less than 4 h of athletic training per week, or being younger than 18.

The sample size calculation is based on differences between the waiting-list control group (WC) and one of the treatment groups (PST or MI) after the intervention. Based on previous research, we assume medium effect sizes of d = .6 [39]. Testing one-sided, given that α = .05 and a power of 80 %, we would need 108 participants (36 for each group) to be able to detect the effect.

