### Study design and group allocation

Figure 1 shows an overview of the procedure (parallel group design). After a first contact and checking for inclusion and exclusion criteria (time 0), athletes will be stratified for gender, sport, and performance level, then randomly assigned to either the PST group, the MI group, or the WC group, and will be informed about their experimental condition. Members of the same team (i.e., curling, volleyball, or hockey) will be assigned to the same intervention group. For randomization, a computer-generated random-number sequence will be prepared in advance and sealed in opaque, consecutively numbered envelopes by an independent researcher. An independent researcher will open the envelopes in sequence based on client number, to determine the participant’s assignment to the groups.

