### Description of the PST and MI intervention

The PST intervention will be adapted from PST programs like Ebersbächer’s *Mental Training* [15]. It involves the practice of four psychological skills (self-talk, imagery, goal-setting, and arousal control) and will be based on the latest guidelines and recommendations about instruction and application of these skills [1, 27, 73, 77]. A sport psychologist trained in specialized PST interventions will explain the expected sport-specific benefits to the participating athletes and advise athletes to do homework between group sessions.

The MI will be adapted from mindfulness-intervention programs, including Mindfulness-Acceptance-Commitment (MAC) [25], Acceptance and Commitment Therapy (ACT) [38], and Mindfulness-Based Stress Reduction (MBSR) [45]. A sport psychologist trained in specialized mindfulness-based interventions will explain the expected sport-specific benefits to the participating athletes and advise athletes to do formal and informal mindfulness practices at home between group sessions.

The interventions will be realized in groups of six athletes each, leading to six sub-groups in each condition (6 × 6 = 36 athletes, see power analysis). A manual will accompany the instructions for the interventions. All components of both interventions must be administered according to the manual’s specifications. Two independent raters will evaluate the adherence to each intervention on the basis of video recordings. In addition to psycho-education and practice at home guided by audio files that can be played on computers or portable devices such as smart phones. All participants will also be provided with a calendar of their exercises to tick off as they are completed, and daily text messages will remind them to practice their PST or mindfulness exercises. Each intervention consists of four 2-h sessions over the course of 5 weeks. Participants will be advised to practice daily and record their amount of practice. All sessions will conducted at the center for elite sports of the Swiss Federal Institute of Sport.

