### Statistical analysis

All analyses will be conducted as intent-to-treat. To assess if randomization is successful in balancing demographic characteristics across the treatment groups, we will compare age, use of psychological skills, mindfulness, and performance level using Student’s t-tests. Two-way (group x time) repeated measures ANOVAs will be used to answer the question regarding whether the intervention (independent variable) had an effect on the primary and secondary outcome measures (dependent variables). Significant overall effects will be followed up with post hoc tests and contrasts between intervention programs (e.g., PST and MI together compared to the WC group). Significance levels will be set at *p* = .05. If there are significant differences between different intervention sub-groups, we will perform multilevel analyses. To test the mediation and moderation models, we will follow the requirements for mediation and moderation suggested by Hayes [36]. The first three authors of this manuscript will have access to the full dataset.

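### Clustering by team and delivery sub-group is modelled only after a significant pre-test, so the overall group x time test exceeds 5% false positives if changes in FAB are correlated within clusters

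*Protocol article*

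**What the plan says.** Four places in the Method section of the protocol article bear on this.

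- Allocation (Study design and group allocation): "Members of the same team (i.e., curling, volleyball, or hockey) will be assigned to the same intervention group". Tennis is not in that list, so tennis players are allocated singly.
- Delivery (Description of the PST and MI intervention): "The interventions will be realized in groups of six athletes each, leading to six sub-groups in each condition".
- Analysis (Statistical analysis): "Two-way (group x time) repeated measures ANOVAs will be used to answer the question" of whether the interventions affected the primary and secondary outcomes. The test is at the .05 level, and post hoc tests and contrasts follow a significant overall effect. Clustering appears once, as a conditional step: "If there are significant differences between different intervention sub-groups, we will perform multilevel analyses".
- Sample size (Participants and power analysis): "The sample size calculation is based on differences between the waiting-list control group (WC) and one of the treatment groups", with "we assume medium effect sizes of d = .6" and "Testing one-sided, given that α = .05 and a power of 80" %, leading to "we would need 108 participants (36 for each group"). No allowance for clustering is mentioned.

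**The concern.** There are two sources of dependence. Teammates share an arm by design and may rate FAB in the same match, against the same opponent and with the same score. Athletes in PST and MI also share a delivery sub-group and its trainer. An ANOVA that counts 108 independent athletes then uses too small an error term for the comparison of arms.

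The conditional step does not cure this, for two reasons.

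- It lets a significance test decide whether the design is respected. With a handful of sub-groups of six, failure to reject is weak evidence of independence.
- It looks only at intervention sub-groups. The team, which is the unit of allocation in three of the four sports, is neither tested nor modelled. Waiting-list athletes have no delivery sub-group before T2, so any team clustering in that arm is out of reach of the rule.

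At stake is the error rate of the overall test, on which the primary claim that PST and MI promote FAB depends.

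**Working it through.** **1. The plan's own figure.** Inputs from Participants and power analysis: d = 0.6, one-sided α = 0.05, power 80%. A two-sample t-test with 36 per arm has 70 df and noncentrality 0.6 × √(36/2) = 2.546, which gives power 80.9%. The stated 36 per arm (3 × 36 = 108) is thus reproduced, as a calculation for fully independent athletes (design effect 1).

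**2. What the primary test is.** The waiting list is assessed at T1 and T2 only, so the three-arm group x time test is a one-way ANOVA of the T2 − T1 change. Stable differences in level between teams cancel. The ICC that matters is that of change.

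**3. Assumptions not in the article.** The ICC of change ρ is set to 0, 0.01, 0.05, 0.10 and 0.20. Each arm has six clusters of six. This is the article's delivery layout for PST and MI, but an assumption for teams and for the waiting list.

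**4. Power of the pre-test.** The wording is read as a test across the 12 sub-groups of the two interventions, an F-test on 2 × 5 = 10 and 12 × 5 = 60 df. Its 5% critical value is 1.993. Under clustering the F ratio is scaled by 1 + 6ρ/(1 − ρ), so power = P(F(10,60) > 1.993 / [1 + 6ρ/(1 − ρ)]).

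| ρ | scale factor | pre-test power |
|---|---|---|
| 0.05 | 1.316 | 16% |
| 0.10 | 1.667 | 31% |
| 0.20 | 2.500 | 63% |

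**5. False-positive rate of the planned rule.** This was simulated with no true effect. If the pre-test is significant, arms are compared at cluster level with F(2,15), which stands in for the multilevel analysis in a balanced layout. Otherwise the ordinary F(2,105) is used.

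| ρ | plain ANOVA | planned rule | planned rule, waiting list unclustered | always at cluster level |
|---|---|---|---|---|
| 0 | 5.0% | 4.6% | 4.8% | 5.0% |
| 0.01 | 5.8% | 5.5% | 5.2% | 5.0% |
| 0.05 | 9.1% | 8.0% | 6.8% | 5.0% |
| 0.10 | 13.7% | 10.0% | 7.6% | 4.9% |
| 0.20 | 22.8% | 10.7% | 8.1% | 5.0% |

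Repeat runs agree within about 0.3 percentage points. Plain ANOVA and the last column have all arms clustered.

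**6. Other readings of the trigger.** If the pre-test is pooled over 18 clusters in all three arms, its power rises to 19%, 40% and 77% at ρ = 0.05, 0.10 and 0.20. The planned rule then rejects in 7.6%, 8.9% and 8.1%.

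**7. Power once clustering is always modelled.** The design effect is 1 + 5ρ. A one-sided cluster-level t-test of one intervention against the waiting list has 10 df, critical value 1.812 and noncentrality 0.6 × √(18/(1 + 5ρ)).

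| ρ | design effect | noncentrality | power |
|---|---|---|---|
| 0.05 | 1.25 | 2.277 | 68% |
| 0.10 | 1.50 | 2.078 | 61% |
| 0.20 | 2.00 | 1.800 | 51% |

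**The case against.** The best defence is that the authors foresaw sub-group clustering and named multilevel analysis as the remedy, and that this step does real work. At ρ = 0.20 it brings the error from about 23% to about 11%, and at ρ = 0.30 the pre-test has 84% power and the rule rejects in 8.6%. That stands, but the rule still does not return to 5% at any positive ICC examined.

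Three stronger readings are tempting, and the article does not support them.

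- *That the error rate exceeds 5% regardless.* It does so only if changes in FAB are positively clustered. The article reports no ICC, and stable team differences drop out of a change score. At ρ = 0 the rule is slightly conservative.
- *That each comparison of PST or MI with the waiting list is inflated to the same degree.* The plan reaches contrasts only after a significant overall effect. With that order kept, a false PST claim against the waiting list occurs in about 4.0%, 5.2% and 5.7% of trials at ρ = 0.05, 0.10 and 0.20. The clear excess lies in the overall test.
- *That the pre-test is nearly blind.* Testing one arm alone, F(5,30), would give 12%, 21% and 43% power. The wording points to the sub-groups of both interventions, hence 16%, 31% and 63%.

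The cluster layout is also uncertain. The article does not say how many teammates enrol, and tennis players are clusters of one, so six equal clusters in every arm lies towards the unfavourable end. Larger team clusters would go the other way: three of 12 per arm, also an assumption, gives 11.3%, 13.7% and 11.2% with the pre-test pooled over all arms.

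**Conclusion.** The concern holds in conditional form. The design creates clusters through allocation and through delivery. The stated analysis models them only after a pre-test that leaves out teams and misses moderate clustering more often than not. If changes in FAB are positively correlated within clusters, the overall test does not hold its 5% level: the rate is about 8% to 11% for an ICC of change between 0.05 and 0.20 with all arms clustered, and about 7% to 8% with an unclustered waiting list. At 0.01 the excess is negligible.

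The direction follows from the text. The size rests on the assumed ICC, the assumed six clusters of six, and the use of a cluster-level F-test to represent the multilevel step. This is a defect in a rule the article states, not a detail left to a fuller plan. It should be corrected before analysis because it affects the primary conclusion.

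**What to change.** Delete the conditional sentence in Statistical analysis. Make a linear mixed model the primary analysis whatever any pre-test shows, with:

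- a random effect for team in all three arms, each tennis player being a cluster of one;
- a random effect for delivery sub-group in PST and MI;
- a single cluster term where team and sub-group coincide, since the two could not be separated with so few clusters;
- Satterthwaite or Kenward-Roger degrees of freedom.

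Because the dependence at issue is in change, the cluster terms must act on the change or on the cluster-by-time effect. A random intercept for level alone would not be enough. Carry the same terms into the secondary, mediation and moderation analyses.

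The text change is small. Allocation and delivery require knowing each athlete's team and sub-group, although the article does not say that both are kept as analysis variables; this should be confirmed. The real cost is precision. Intervals widen, and the 80% power, computed for independent athletes, must be restated (about 68%, 61% and 51% under the assumptions above). Holding the planned power by the design effect alone would take 36 × (1 + 5ρ) per arm, which is 45, 54 or 72 at ρ = 0.05, 0.10 or 0.20, before any allowance for few clusters. If the sample cannot grow, the lower power should be stated.

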## Discussion

This study is the first to examine the effectiveness both PST and MI in the same randomized controlled trial. We will assess FAB as the primary outcome measure of this study; however, we also investigate psychological variables that may negatively influence FAB (i.e., competition anxiety, negative outcome expectations, and cognitive interference) and objective and subjective measures of performance as secondary outcome variables.

Both interventions are hypothesized to improve FAB and reduce the extent of psychological variables that may prevent FAB compared to a waiting-list control group. If the interventions are effective, both PST and MI may be considered empirically validated methods to help athletes behave functionally, which can be considered a prerequisite for performing optimally. This study may also fill a gap in sport psychology research, considering the current lack of randomized controlled trials. Besides investigating the effectiveness of the two interventions, the current study intends to examine potential mechanisms of change and moderators of outcome. Therefore, we will hopefully not only be able to answer the question whether the interventions work, but also how, under what conditions, and for whom.

While the question of how to perform optimally in competition or a game is not the only reason why athletes seek the advice of a sport psychologist,^6^ it is a very common, perhaps even the most common reason [30]. The frequency of this issue being presented underlines the importance of defining FAB as construct and operationalizing it as an outcome measure of sport psychological interventions. Assessing FAB might also help to solve the problem that in researching sport psychological interventions, an abundance of outcome variables is used, which makes it difficult to compare different sports. Also because objective parameters of athletic performance are heavily influenced by physical and external factors, using FAB as an outcome is an attractive alternative. The use of the ambulatory-assessment method has the advantage of being very close to what athletes are actually doing and experiencing in games or competitions (i.e., a high external validity). The critical points of this method include the fact that it is time-consuming and hardly explored in sport psychology. As in other forms of real live measurements [51], the chosen method should be sufficiently brief to minimize interference with athletes’ behavior and prevent jeopardizing optimal performance. In subsequent studies, one could expand the assessment of FAB via ambulatory assessment by having athletes rate video recordings of behavioral sequences within the ongoing competition. Real live measurement is an increasingly used assessment method that offers many additional research options in (elite) sport.

Future studies might use the presented study protocol to examine the effect of PST and MI on other psychological phenomena that may disturb or facilitate FAB and that are not part of the current study, for example, rumination over mistakes. As we assume FAB to be important in every sport (i.e., FAB is not sport-specific), investigating FAB in other sports (e.g., gymnastics, athletics, freestyle ski and snowboard, golf, or basketball) could be a next step. Furthermore, future research may gainfully examine other personality traits potentially influencing (i.e., moderating) athletic performance, such as perfectionism [69], narcissism [60], or intrinsic motivation [78].

## Abbreviations

AAQ-II, acceptance and action questionnaire; ACT, acceptance and commitment therapy; AMQ, athletic mindfulness questionnaire; ANT, attention network test; BSI, brief symptom inventory; CAI-S, competition anxiety inventory state; DSS, decentering scale for sport; EQ, experience questionnaire; FAB, functional athletic performance; FFMQ-SF, five facets mindfulness questionnaire short form; GSI, global symptom index; MAC, mindfulness-acceptance-commitment; MBSR, mindfulness-based stress reduction; MI, mindfulness-based interventions; PST, psychological skills training; RCT, randomized controlled trial; RSC, Rosenbergs’s self-esteem Scale; SCS, self compassion scale; SEC-27, self-assessment of emotional competencies; TEOSQ, task ego orientation sport questionnaire; TOPS, test of performance strategies; TOQS, thought occurrence questionnaire sport; WC, waiting-list control group
